**Fig. 2 Fig2:**
[figure not shown]
Content for the schedule of enrollment, interventions, and assessments

### Patient recruitment and eligibility

The 84 patients included in the study will be recruited from several municipalities in the Zealand Region and Capital Region of Denmark in the period between August 2017 and August 2018. Before the beginning of the study the case managers at the municipalities will receive study training to be able to inform about the study and apply the inclusion criteria to each identified patient. Patients are eligible if they: (1) are aged 16–60 years; (2) suffer from an ABI; (3) acquired the injury within the last 3–24 months; (4) are employed or enrolled in education prior to the injury; (5) are currently employed or enrolled in education up to a maximum of 15 h/week or taking sick leave/unemployed; (6) have the motivation to participate in VR; (7) are able to participate in group sessions; (8) are able to speak and understand Danish; and particularly for the family intervention, (9) have at least two family caregivers willing to participate in the study. Individuals are excluded from the study if they: (1) have any other somatic or psychiatric illnesses before the ABI that make it impossible to complete the intervention; (2) suffer from substance abuse or severe apasia; (3) have a progressive brain injury; (4) are pregnant; and particularly for the family intervention, (5) have a mini mental state examination score < 23. All individuals that meet the inclusion criteria will be invited to enroll in the study and will be asked for consent to participate.

All patients in the intervention group will not receive usual care from the municipalities. However, they will not be stopped from participating in leisure activities or private practice treatment if they prefer this during the intervention period.

### Randomization

To avoid confounding between the VR intervention and the control group due to random probability, the number of cases and controls within each of the enrolled municipalities is set to be the same (+1/–1). Due to the prospective nature of the inclusion, which practically means that the number of patients included within each municipality is not known a priori, the randomization is performed by randomly assigning the first patient within each municipality to either the VR intervention or the conventional VR program. The following patient (within each municipality) is then assigned consecutive to the other group and so forth. This randomization scheme ensures equal distribution of cases and controls, both within each municipality as well as in time, avoiding confusion of these two factors. Controlling the distribution over time is central in such a study where some variation over the trial period due to protocol familiarity of the rehabilitation team at the Brain Injury Centre may be expected.

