**Methods:**

This study is an interventional, two-arm, six-month follow-up, cluster randomized controlled trial involving four municipalities in the Zealand Region and the Capital Region of Denmark. A total of 84 patients with ABI evenly distributed across four municipalities will be included in the study. The patients will randomly be allocated in a 1:1 ratio to the VR intervention provided by a specialized Brain Injury Centre or the conventional VR provided by the municipalities (usual care). The six- to nine-month intervention will consist of individual and group therapies as well as a work placement program including supported employment. Furthermore, the intervention will include a family intervention program followed up by support to one individual family caregiver. The primary outcomes are increased work or study rate at six-month follow-up. Moreover, a budget impact analysis and possibly a cost-utility analysis of the intervention will be performed.

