## Methods/Design

### Trial design and hypotheses

An interventional, two-arm, six-month follow-up, cluster RCT (Fig. 1) including 84 participants with an ABI allocated randomly (allocation ratio 1:1) to the VR intervention and control group that consists of a conventional VR program (usual care).

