### A description of the manual-based VR interventions

This manual-based VR study comprises the following three phases:Initial assessment: Within two weeks after the referral to the study, each patient will meet with the case manager in the municipality (brain injury coordinator). Here, a more thorough interview will ensure that the inclusion criteria are met and, in addition, asses the patient’s readiness for VR. Moreover, the participant will be fully informed about the content of the study, how participation is voluntary, and how they are free to withdraw at any time during the study. If written informed consent is obtained, each patient is assigned a unique trial ID number and baseline questionnaires will be filled out together with the following socio-demographic, employment, and clinical data: gender; date of birth; residence; civil status; nationality; income; pre-injury employment and education status; pre-injury occupation status; length of education; time since the brain injury; type and location of the brain injury; number of days hospitalized; the date of discharge; clinical diagnoses or any relevant medical events; and alcohol consumption or abuse. Participants will then be randomly assigned to either the VR intervention or the conventional VR. At last, each patient included in the VR intervention group will be asked to choose at least two family members to participate in the family intervention and one family caregiver which will participate actively in the individual sessions and serve as future support and resource facilitator to assist them in returning to work. This initial assessment will take approximately 50 min and the patient will have the opportunity to ask questions throughout the entire assessment. To exclude recruitment bias, patients that meet the eligibility criteria but refuse to participate in the study will be asked a few questions about their refusal. Hereafter, the patient will be contacted by external testers and baseline testing will be completed.The VR intervention program: The VR intervention lasts for a total of 6–9 months and consists of, first, six different modules (approximately three months) that are individually planned based on the patient needs and goals and, second, a work placement program (approximately 3–6 months). To ensure a uniform procedure of each of the different modules, comprehensive “standard operating procedures” (SOPs) will be developed by the rehabilitation team at the Brain Injury Centre before the beginning of the VR intervention. All members of the rehabilitation team (which includes six neuropsychologists, eight occupational therapists, and four physiotherapists) are already experienced in the VR intervention program and exceedingly specialized in ABI rehabilitation. They will go through a one-day workshop to be thoroughly introduced to the specific study protocol and the SOPs as recommended by Holmes et al. [31]. The six modules will be grouped into: (1) individual therapies, which includes neuropsychological sessions (10 h), balance between work and everyday life (20 h), and job matching (10 h); (2) grouped-based therapies, which includes psycho education (18 h), mindfulness (15 h), and physiotherapy training (15 h); (c) a manualized family intervention program (eight sessions of 90 min) [32] and an individual caregiver coaching, supporting the caregiver in assisting the patient using the different strategies and tools learned in the intervention in everyday life and at the workplace (12 h); (4) an individual work placement program including work practice (3–6 months), supported employment where the rehabilitation team is at the work place (30 h), and the development of a post-rehabilitation plan (4 h). The modules are planned based on the participant’s needs and goals thus, the length, duration, structure, and composition of the program will vary from patient to patient. The individual sessions and group sessions are delivered either in parallel or in serial depending on the patient.Group sessions will take place at the Brain Injury Centre BOMI and the individual sessions will most often take place in the patient’s home. The individual work placement intervention will take place at relevant workplaces, the patient’s current workplace, or at a new workplace found by the municipality or the Brain Injury Centre BOMI, depending on the individual case.Post-trial evaluation: An evaluation of the VR intervention will be performed by a self-developed semi-structured interview of each patient. Here, questions related to the recruitment procedure, the modules of the study, the timing of modules, and the coaching by the rehabilitation team will be collected. Furthermore, all case managers at the municipalities that referred participants to the study will be asked about their experiences and level of satisfaction.

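### Only the first patient in each municipality is randomised; the other 80 of 84 allocations alternate and are predictable to the case managers who select patients

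*Protocol article*

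**What the plan says.** The abstract states that "The patients will randomly be allocated in a 1:1 ratio", and Trial design and hypotheses describes participants as "allocated randomly (allocation ratio 1:1) to the VR intervention and control group".

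The Randomization section gives the actual procedure. The first patient in each municipality is assigned at random. Then "The following patient (within each municipality) is then assigned consecutive to the other group and so forth". The stated reasons are to keep the arms equal to within one patient in each municipality and to spread both arms evenly over time, because the rehabilitation team may change as it becomes familiar with the protocol.

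The people who bring patients into the trial are municipal case managers:

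- Under Patient recruitment and eligibility they are trained to inform patients and to "apply the inclusion criteria to each identified patient". The criteria include motivation for vocational rehabilitation and ability to take part in groups.
- In the initial assessment (A description of the manual-based VR interventions) the patient meets the case manager, and "a more thorough interview will ensure that the inclusion criteria are met". Readiness for rehabilitation is judged at the same meeting. Consent, baseline questionnaires and assignment follow, and patients assigned to the intervention then name their family members.
- Under the usual-care section they refer patients and complete a questionnaire on each participant at the start, at the end and at six months. The municipality itself delivers the control programme.

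The Blinding section covers research assistants at data entry, the researchers and the statistician. It does not cover case managers.

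**The concern.** Strict alternation after one random start is not random allocation of patients. Anyone who knows what the previous patient in the municipality received knows what the next one will receive. Treatment is open, and the rule is published.

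The case manager decides whom to refer and when, and applies entry criteria that leave room for judgement. Someone who knows that the next place is an intervention place can, without any bad intent, bring forward a patient who seems ready for work, or hold back one who does not. The arms would then differ in prognosis before treatment begins. Motivation and readiness, the most likely routes, are not among the baseline data listed for collection, so the planned covariate adjustment would not remove that part of the bias.

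What is at stake is the primary comparison of weekly hours at work or study: a difference could reflect who was referred rather than what was delivered.

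**Working it through.** **Inputs.** 84 patients, 42 + 42 (Sample size and power). Four municipalities: "A total of 84 patients with ABI evenly distributed across four municipalities will be included in the study" (Abstract), hence 84 / 4 = 21 each. One random assignment per municipality, then alternation (Randomization). Variance equal to 4 times the mean, control mean 10 h, intervention mean 14 h (Sample size and power).

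**1. The plan's balance claim.** Alternation over 21 patients gives 11:10 or 10:11, so the promised difference of at most one per municipality is met. This part of the plan works as stated.

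**2. How much is random.** With k municipalities, k allocations are random and 84 − k are determined.

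| Municipalities | Random | Determined | Share |
|---|---|---|---|
| 2 | 2 | 82 | 98% |
| 4 (Abstract) | 4 | 80 | 95% |
| 6 | 6 | 78 | 93% |
| 12 | 12 | 72 | 86% |

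The range is shown because the recruitment section says only that patients "will be recruited from several municipalities in the Zealand Region and Capital Region of Denmark".

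**3. Predictability.** A person who knows the earlier allocations is right for all 20 later patients in a municipality and half the time for the first: 4 × 20.5 = 82 correct guesses of 84. For comparison, simulated with four sites of 21 (the guess is always the arm that is behind):

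| Scheme | Determined if block sizes known | Correct guesses of 84 |
|---|---|---|
| Alternation | 80 | 82 |
| Blocks of 2 | 40 | 62 |
| Blocks of 4 | 27 | 59 |
| Blocks of 4 and 6, random order | 22 | 57 |

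**4. Randomness behind the test.** Four random starts allow 2^4 = 16 allocation lists. The smallest attainable p-value of a randomisation test is 1/16 = 0.0625 one-sided and 2/16 = 0.125 two-sided. With five municipalities it is 1/32 = 0.031 and 0.0625; with six, 1/64 = 0.016 and 0.031. The plan does not propose such a test. The calculation only shows how little the allocation itself supports a claim of P < 0.05.

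**5. What selection could do.** Let δ be the difference in mean prognosis between arms, in SD units, with no true treatment effect. For an unadjusted two-sided 5% test with 42 per arm, the rejection rate is about Φ(δ√21 − 1.96) + Φ(−δ√21 − 1.96), where √21 = √(42/2) = 4.583. The protocol states no SD; its variance assumption implies √(4 × 10) = 6.3 h in the control arm.

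| δ (assumed) | In hours | δ√21 | Normal formula | Simulated (20,000 trials) |
|---|---|---|---|---|
| 0.1 | 0.6 | 0.458 | 0.074 | 0.074 |
| 0.2 | 1.3 | 0.917 | 0.150 | 0.148 |
| 0.3 | 1.9 | 1.375 | 0.280 | 0.27 |

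A shift of 0.2 SD is 1.3 / 4, about a third of the 4 h difference used in the power example.

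**The case against.** The strongest reply has four parts.

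*Nothing says the case managers know the sequence.* The article does not state who applies the rule, how many case managers a municipality has, or whether they share earlier allocations. That is true, and predictable from the previous allocation is the exact description. A municipality with several case managers who do not communicate would be less exposed. But the municipality treats each control, intervention patients leave its usual care, and assignment falls within the case manager's own initial assessment. Knowledge of the last arm is the natural expectation.

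*There are safeguards.* Assignment comes after consent and baseline questionnaires, everyone eligible is to be invited, the interview takes place within two weeks of referral, and patients who refuse are asked why. These limit how freely patients can be reordered. None hides the next arm, and none captures a patient who was deferred, judged not ready or never referred. The Discussion also relies on cluster randomisation against contamination, yet every municipality contributes patients to both arms.

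*The error rates are illustrations.* They are unadjusted, and the documents give no basis for a particular δ. The plan measures hours at baseline and models repeated measures with covariates such as age, severity and site, so a shift visible in those would be partly corrected. This stands: only bias through unrecorded characteristics is beyond repair.

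*The balance was chosen for a reason.* It was, and the reason is sound. It does not require alternation.

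Leaving detail to a fuller protocol is no answer here. The article states the rule outright, and no concealment procedure can hide an alternating sequence.

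**Conclusion.** The concern holds and should be corrected before the trial relies on its allocation. As written, with four municipalities, 80 of 84 allocations (95%) are fixed by the one before, and at least 72 (86%) are fixed for any number of municipalities up to 12. Describing the patients as randomly allocated is not accurate under this rule.

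The count follows directly from the text. That recruiters know the previous arm is a well-supported inference from their role and the open design. The size of any resulting bias is unknown. The figures of about 7%, 15% and 27% false positives rest on assumed prognostic shifts of 0.1, 0.2 and 0.3 SD and an unadjusted comparison.

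**What to change.** Replace alternation with a computer-generated list, stratified by municipality, in permuted blocks of randomly varying size, for example 4 and 6. A person outside both the municipalities and the rehabilitation team should hold the list and release each allocation only after eligibility, consent and baseline are recorded. The external baseline testing, now placed after assignment, should come before release. Case managers should not know the block sizes. Amend the Randomization section accordingly, and remove the term cluster from the design description, since individuals within a municipality go to both arms.

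The cost is one list, a release step (telephone, web or sealed sequence) and an amendment. Balance by municipality and over time is kept, somewhat more loosely. With blocks of at most 6, the imbalance within a municipality cannot exceed 3. Even the extreme case of 3 in the same direction in all four sites gives 48:36, and the variance of the difference then rises by (1/48 + 1/36) / (2/42) = 1.02, or 2%.

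The article appeared in August 2017, the month recruitment was due to start, so some patients may already have been allocated by alternation. They should stay in the trial. The date of the change should be recorded, the allocation method reported for each period, and the primary analysis repeated on patients allocated under the new list. If the rule is not changed, the report should describe allocation as alternation from a random start and state selection bias as a limitation.

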### Blinding

Because of the nature of the study, it will be clear to most participants whether they are allocated to the VR intervention or the control group. Thus, it is not possible to blind either the participants or the rehabilitation team, but they will be asked not to disclose any details about the allocation or the content of the VR. The two independent research assistants will be trained to administer the assessments and will be blinded to the allocation when entering data into the database. The researchers and the statistician performing the data analysis are blind to the treatment arm in which the participants are allocated. The rehabilitation team and the research assistant will only be involved in the data collection and will therefore not participate in the data analyses.

### A description of the manual-based VR interventions

This manual-based VR study comprises the following three phases:Initial assessment: Within two weeks after the referral to the study, each patient will meet with the case manager in the municipality (brain injury coordinator). Here, a more thorough interview will ensure that the inclusion criteria are met and, in addition, asses the patient’s readiness for VR. Moreover, the participant will be fully informed about the content of the study, how participation is voluntary, and how they are free to withdraw at any time during the study. If written informed consent is obtained, each patient is assigned a unique trial ID number and baseline questionnaires will be filled out together with the following socio-demographic, employment, and clinical data: gender; date of birth; residence; civil status; nationality; income; pre-injury employment and education status; pre-injury occupation status; length of education; time since the brain injury; type and location of the brain injury; number of days hospitalized; the date of discharge; clinical diagnoses or any relevant medical events; and alcohol consumption or abuse. Participants will then be randomly assigned to either the VR intervention or the conventional VR. At last, each patient included in the VR intervention group will be asked to choose at least two family members to participate in the family intervention and one family caregiver which will participate actively in the individual sessions and serve as future support and resource facilitator to assist them in returning to work. This initial assessment will take approximately 50 min and the patient will have the opportunity to ask questions throughout the entire assessment. To exclude recruitment bias, patients that meet the eligibility criteria but refuse to participate in the study will be asked a few questions about their refusal. Hereafter, the patient will be contacted by external testers and baseline testing will be completed.The VR intervention program: The VR intervention lasts for a total of 6–9 months and consists of, first, six different modules (approximately three months) that are individually planned based on the patient needs and goals and, second, a work placement program (approximately 3–6 months). To ensure a uniform procedure of each of the different modules, comprehensive “standard operating procedures” (SOPs) will be developed by the rehabilitation team at the Brain Injury Centre before the beginning of the VR intervention. All members of the rehabilitation team (which includes six neuropsychologists, eight occupational therapists, and four physiotherapists) are already experienced in the VR intervention program and exceedingly specialized in ABI rehabilitation. They will go through a one-day workshop to be thoroughly introduced to the specific study protocol and the SOPs as recommended by Holmes et al. [31]. The six modules will be grouped into: (1) individual therapies, which includes neuropsychological sessions (10 h), balance between work and everyday life (20 h), and job matching (10 h); (2) grouped-based therapies, which includes psycho education (18 h), mindfulness (15 h), and physiotherapy training (15 h); (c) a manualized family intervention program (eight sessions of 90 min) [32] and an individual caregiver coaching, supporting the caregiver in assisting the patient using the different strategies and tools learned in the intervention in everyday life and at the workplace (12 h); (4) an individual work placement program including work practice (3–6 months), supported employment where the rehabilitation team is at the work place (30 h), and the development of a post-rehabilitation plan (4 h). The modules are planned based on the participant’s needs and goals thus, the length, duration, structure, and composition of the program will vary from patient to patient. The individual sessions and group sessions are delivered either in parallel or in serial depending on the patient.Group sessions will take place at the Brain Injury Centre BOMI and the individual sessions will most often take place in the patient’s home. The individual work placement intervention will take place at relevant workplaces, the patient’s current workplace, or at a new workplace found by the municipality or the Brain Injury Centre BOMI, depending on the individual case.Post-trial evaluation: An evaluation of the VR intervention will be performed by a self-developed semi-structured interview of each patient. Here, questions related to the recruitment procedure, the modules of the study, the timing of modules, and the coaching by the rehabilitation team will be collected. Furthermore, all case managers at the municipalities that referred participants to the study will be asked about their experiences and level of satisfaction.

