**Fig. 1 Fig1:**
[figure not shown]
A *flow chart* of the study

The main objective of the study is to develop an individually targeted manual-based VR program and determine its efficacy for patients with ABI. The first hypothesis of the study is that more participants allocated to the VR intervention group will have a significant higher employment or study rate (measured in hours) at six-month follow-up when compared to participants receiving the conventional VR program provided by the municipalities (control group). The second hypothesis is that health-related quality of life (HRQoL) and disability among the participants and HRQoL and the caregiver burden among the caregivers are significantly improved at the end of the VR intervention and at six-month follow-up when compared to the conventional VR program. Finally, a budget impact and possibly a cost-utility analysis will be performed since we hypothesize that it will be an economically sound decision for the municipalities to invest in a specialized VR when compared to the conventional VR program provided by the municipalities. Such an analysis is based on an overall assessment of the health gain, both in terms of clinical effects and participant perceived utilities, and the related expenditures and costs.

The duration of the study is three years and the assessments will take place at baseline and at the end of the intervention (approximately after 6–9 months). In order to determine any long-term effect of the intervention, follow-up assessment is planned after six months.

The trial is designed and reported according to the SPIRIT (Standard Protocol Items: Recommendations for Interventional Trials) Statement [30] (see Additional files 1 and 2 and Fig. 2).

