
### The conventional VR provided by the municipalities (usual care)

Individuals allocated to the control group will receive the conventional VR program provided by the municipalities over the same period of time. Thus, the participants in the control group will receive VR support by the local municipal authority that may vary in content and intensity. As for the intervention group, each individual in the control group will select a family caregiver that will go through the same questionnaires as the caregivers in the VR intervention group regarding HRQoL and functional level.

Furthermore, the case manager at the municipalities is obliged to: (1) refer patients to the study; (2) hand out the baseline questionnaires to the participants and their family caregivers; and (3) complete a questionnaire about each participant at the beginning and end of the study, and again at the six-month follow-up.

An evaluation of the conventional VR provided by the municipalities will be performed by the rehabilitation team using a self-developed semi-structured interview of each patient.

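### The caregiver compared between arms is chosen after open allocation and for a different role in each arm, so randomisation does not protect the caregiver comparison

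*Protocol article*

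**What the plan says.** All places are in the protocol article.

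- **Hypothesis** (Trial design and hypotheses). The second hypothesis includes a between-arm claim about caregivers: "HRQoL and the caregiver burden among the caregivers are significantly improved", relative to conventional rehabilitation, both when the intervention ends and six months later.
- **Outcomes** (Table 1). Five rows of caregiver outcomes, including the Caregiver Burden Scale, are measured at baseline, end of intervention and six months.
- **Order of events** (A description of the manual-based VR interventions, initial assessment). Consent and baseline questionnaires come first. Then "Participants will then be randomly assigned to either the VR intervention or the conventional VR". Only after that, as the last step, are intervention patients asked to choose relatives: "each patient included in the VR intervention group will be asked to choose at least two family members to participate in the family intervention". The same sentence asks them for a further choice, namely "one family caregiver which will participate actively in the individual sessions and serve as future support and resource facilitator".
- **Control arm** (The conventional VR provided by the municipalities). Here "each individual in the control group will select a family caregiver that will go through the same questionnaires as the caregivers in the VR intervention". No other task is given to this person.
- **Blinding.** The article accepts that "it will be clear to most participants whether they are allocated to the VR intervention or the control group".
- **Eligibility** (Patient recruitment and eligibility, inclusion criterion 9). Patients need at least two family caregivers willing to take part, a criterion attached particularly to the family intervention.

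**The concern.** Randomisation makes two groups comparable only for people who are defined before allocation. The patients are. The caregivers, as written, are not: each is picked by a patient who mostly knows the arm, and for a different job. An intervention patient chooses someone for 12 h of coaching and continuing support at home and at work, alongside a family programme of eight 90-minute sessions. A control patient chooses someone to fill in forms. The same patient could well name a different relative under the two requests.

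If so, the arms may differ in caregiver burden or quality of life before any treatment has acted, and that difference would be read as an effect. No later analysis can fully restore comparability between caregivers selected under arm-specific demands. It has to be settled in the enrolment procedure, so it is not a detail that an analysis plan could supply.

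**Working it through.** **Step 1. Is the choice made after allocation?** In the intervention arm, yes: the initial-assessment text lists consent, baseline questionnaires, random assignment and then the choice of relatives. In the control arm the choice is described as one made by people allocated to control. No date is given, but the natural reading is that it also follows allocation.

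**Step 2. Is the request the same in both arms?** No. The intervention request is for family-programme participants and one active supporter. The control request is for a questionnaire respondent.

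**Step 3. Does another rule fix the person beforehand?** Inclusion criterion 9 is checked before randomisation and establishes that two willing caregivers exist. It does not say which of them, or whether either of them, supplies the Table 1 outcomes.

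**Step 4. When is the caregiver baseline taken?** Table 1 requires one, and the case manager hands baseline questionnaires to patients and their caregivers. The patient questionnaires precede assignment, whereas the caregiver is named afterwards. So the caregiver baseline is either after allocation or undefined relative to it.

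**Step 5. How much could it matter?** The article gives no caregiver SD, no selection effect and no power figure for caregiver outcomes, so there is no figure of its own to reproduce. The illustration uses:

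- n = 42 per arm (Sample size and power), one caregiver per patient, no losses;
- outcome in SD units, so SD = 1;
- no true effect, unadjusted comparison, two-sided 5% level;
- selection difference d = 0.1, 0.2 or 0.3 SD (**assumption**).

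Standard error of the difference: SE = √(2/42) = 0.218.

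False-positive rate: P = 1 − Φ(1.96 − d/SE) + Φ(−1.96 − d/SE).

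| d (SD) | d/SE | False-positive rate |
|---|---|---|
| 0 | 0 | 5.0% |
| 0.1 | 0.46 | 7.4% |
| 0.2 | 0.92 | 15.0% |
| 0.3 | 1.37 | 28.0% |

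For scale, the difference detectable with 80% power is (1.96 + 0.8416) × 0.218 = 0.61 SD. A selection difference of 0.3 SD would be about half of that (0.3/0.61 = 0.49).

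**The case against.** The best defence is criterion 9. If it applies to every patient, willingness to take part is screened before allocation in both arms, and the pool is already narrowed. This stands as a real limit on the bias. It does not remove it, because choice within the pool remains open and the role still differs by arm.

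A second defence is that Table 1 has caregiver baselines and the Statistical analysis section plans repeated-measures and multilevel models for the primary and secondary outcomes. An adjusted analysis could remove part of a baseline imbalance, so the rates above apply to an unadjusted comparison only. Adjustment is not a clean remedy if the baseline is itself recorded after allocation is known, and it does not deal with relatives whose later course would differ anyway.

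A reader might also infer stronger things that the documents do not support:

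- *Several measured caregivers per intervention patient against one per control patient, with correlated answers treated as independent.* The two or more family members are chosen to attend the family programme and are nowhere called outcome respondents. The control-arm sentence opens by likening that arm to the intervention group, which suggests one measured caregiver per patient in each.
- *Control caregivers complete fewer instruments.* The sentence does describe the content as "the same questionnaires as the caregivers in the VR intervention group regarding HRQoL and functional level", without mentioning burden. But it says the questionnaires are the same, and Table 1 makes no distinction by arm. This is loose wording.
- *The bias favours the intervention.* An active supporter might be a less burdened, more available relative, or might be the main and most burdened carer. The documents do not settle which.
- *The relative-rated MPAI-4 is affected too.* Table 1 speaks only of relatives and does not say that the rater is the chosen caregiver.

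**Conclusion.** The point holds for the caregiver half of the second hypothesis. The person measured is chosen after open allocation and for a different role in each arm, and nothing in the article fixes that person beforehand. A between-arm difference in caregiver burden or quality of life could therefore reflect who was chosen and not what the programme did.

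Neither the size nor the direction of the bias can be derived from the documents. The range of about 7% to 28% rests on assumed selection differences of 0.1 to 0.3 SD, one caregiver per patient, complete data and no adjustment; 28% is the top of that assumed range and not an estimate. The primary outcome, weekly hours at work or study, is untouched. The change should be made, but the trial's main conclusion does not depend on it.

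**What to change.** Amend the initial-assessment text and the usual-care section together:

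1. Before randomisation, every patient names one index caregiver, asked in the same words and by the same rule.
2. The index caregiver completes the Table 1 caregiver baseline at that point, before allocation is revealed.
3. The between-arm caregiver analysis uses the index caregiver, in the arm to which the patient was allocated, whoever later takes the active role.
4. Further family members may join the intervention but do not enter that comparison.

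The cost is small: one question moves ahead of allocation, at a visit where criterion 9 already requires asking about willing caregivers. The content of the intervention does not change. The drawback is that the index caregiver will sometimes not be the person who later becomes the active supporter, in which case the comparison may understate the effect on that supporter. That is the price of a comparison that randomisation protects.
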